## Methods

### Design

For this project, chronic pain, including aching, tenderness, soreness, is defined as persistent or intermittent pain in the ipsilateral upper limb or body for more than 3 months after surgical treatment for breast cancer, that is, beyond the expected period of healing [21-23]. A 12-week, two-arm, parallel randomized controlled trial (Clinical trial registration ID: NCT02462226) has been designed to evaluate the effectiveness of the Web- and mobile-based The-Optimal Lymph-Flow self-care strategies to promote lymph flow versus control Arm Precaution group for managing chronic pain and symptoms related to lymphedema. The data collectors will be blinded to the group assignments. The protocol is in accordance with the CONSORT-EHEALTH (see Multimedia Appendix 1) checklist [24]. Multimedia Appendix 2 presents the full proposal review feedback form. Figure 1 shows the CONSORT-EHEALTH flow diagram for recruitment and randomization [24].

**Figure 1 figure1:**
[figure not shown]
The CONSORT flow diagram.

### Ethical Approval

This study was approved by the Institutional Review Board of NYU Langone Medical Center on June 8, 2015.

### Study Population

Study population includes: (1) patients who have been surgically treated for breast cancer more than 3 months (healing usually occurs within 3 months of surgical treatment for cancer); (2) patients who report *persistent or intermittent* pain, including aching, tenderness, soreness; (3) patients may or may not report any of the symptoms related to lymphedema (ie, swelling, heaviness, tightness, firmness, numbness, tingling, stiffness, limb fatigue, limb weakness, and impaired limb mobility of shoulder, arm, elbow, wrist, and fingers); (4) patients may or may not have a history of lymphedema or have been treated for lymphedema; (5) patients have Internet access to the Web- and mobile-based program at home or willing to access the program using the laptop provided by the researchers at the cancer center; (6) ability to understand and the willingness to sign a written informed consent document.

Exclusion criteria are (1) patients who do not report any pain, including aching, tenderness, and soreness; (2) patients who have known metastatic disease or other bulk disease in the thoracic or cervical regions; (3) patients who have lymphedema due to cancer recurrence; (4) patients with documented advanced cardiac or renal disease.

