Grounded in research-driven self-care behavioral strategies [14,19], The-Optimal-Lymph-Flow [22] is a unique patient-centered Web- and mobile-based educational and behavioral program focusing on self-care strategies to lessen the symptom burden by promoting lymph flow and maintaining optimal BMI, targeting compromised lymphatic system and BMI, that is, risk factors for pain and symptoms related to lymph fluid accumulations. Patients learn self-care stratigies through the Web- and mobile-based program which can be downloaded on computer, laptop, as well as any mobile phones and tablets. Its underlying premise is to empower, rather than inhibit, how breast cancer survivors live their lives by emphasizing “what to do,” rather than “what to avoid.” It features a safe, feasible, and easily-integrated-into-daily-routine self-care strategies that include shoulder mobility exercises to promote shoulder function, muscle-tightening breathing, muscle-tightening pumping exercises, and large muscle exercises to promote lymph flow and drainage, as well as general instructions to encourage nutrition-balanced (more vegetables and fruits), portion-appropriate diet (feeling 75% full for each meal), adequate hydration, and sleep to strive for maintaining optimal BMI. Patients can learn and follow all the exercises through avatar video simulations [14,19]. The efficacy of The-Optimal-Lymph-Flow has been demonstrated in our recently published study of 140 patients who received the face-to-face nurse-delivered program [19]. Findings of the study demonstrated that over 90% of patients improved their limb volume at 12-month follow-up. This system has been used successfully for its usability testing. The preliminary usability tested was completed by 30 breast cancer survivors who evaluated the easiness, difficulties, and feasibility of using the system on computer, iPhone, iPad, or other smartphones or tablets. Findings of the usability and feasibility test have demonstrated that patients love the Web-based program, especially the videos using the avatar technology to demonstrate the complicated lymphatic system and illustrate the physiological functions of each exercise and detailed step-by-step instructions for each exercise.

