### Recruitment

#### Recruitment Process

Participants have been recruited face-to-face at point of care during clinical visits from New York University (NYU) Cancer Center. To accomplish recruitment of 120 participants, we plan to use the successful procedures of recruiting and consenting participants used by the PI and the team in the preliminary studies [3,9,14,17,19]. Successful strategies include the use of *Invitation Flyer* that describes the study. This *Invitation Flyer* is posted on the bulletin boards or breast cancer support website at the cancer center, and is also available in the reception areas of the cancer center, examination rooms, and rooms holding support group meetings. In addition, health care providers such as nurses, oncologists, breast surgeons, and oncology radiologists at the center are willing to refer women meeting the inclusion criteria to the study by distributing the *Invitation Flyer* that describes the study to the potential participants.

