#### Control Arm Precaution Group (n=60)

Patients assigned to the control Arm Precaution group will have access to the website section that emphasizes on precautionary lifestyle behaviors, such as avoidance of repetitive limb movement, lifting weighted objects, needle punctures, blood draw, and the use of compression garments for air travel in the affected limb [20,21]. Patients will have access to the following contents of the website: Lymphedema, Diagnosis of Lymphedema, Risk of Lymphedema, Lymphatic System, 3 avatar videos for Daily Exercises to promote limb mobility, and Arm Precautions. However, patients will not have access to The-Optimal-Lymph-Flow program, including Self-care*,* Daily Exercises to promote lymph flow, and 8 Avatar videos as well as Ask Experts that allows them to email to the researchers about their self-care. Patients will access to the Web- and mobile-based Arm Precaution program and learn about the program and daily exercises to promote limb mobility during the first in-person research visit.

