#### Duration of Intervention

From the previous one-arm clinical trial and usability and feasibility studies on the Web- and mobile-based The-Optimal-Lymph-Flow [19,23], we estimate that it would take about 45-60 minutes for patients to learn all the sections of the program and about 15 minutes to learn the The-Optimal-Lymph-Flow exercises for the intervention group through 8 avatar videos. It takes about 5 minutes to perform a set of The-Optimal-Lymph-Flow daily exercises each time. We encourage patients in the intervention group to perform at least twice a day or more times of the exercises during the study period. Participants in the control group will have access to three limb mobility exercise avatar videos and it takes less than 3 minutes to perform a set of limb mobility exercises each time. Patients in the control group will be instructed to perform limb mobility exercises at least twice a day or more times during the study period.

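### Eligibility neither excludes nor records earlier receipt of The-Optimal-Lymph-Flow, so women already taught the programme can be randomised, which would reduce the contrast between arms

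*Protocol article*

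**What the plan says.** Under Study Population the exclusions are: no reported pain; known metastatic or bulk disease; and, to close the list, "patients who have lymphedema due to cancer recurrence; (4) patients with documented advanced cardiac or renal disease". On time since surgery, the criterion is "patients who have been surgically treated for breast cancer more than 3 months", with no upper limit. Women with a history of lymphedema, treated or not, may enter.

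The Background describes two groups already exposed to the programme. One is "our recently published study of 140 patients who received the face-to-face nurse-delivered program" (reference 19). For the Web and mobile system, "The preliminary usability tested was completed by 30 breast cancer survivors". The section on duration of the intervention draws on the same experience: "From the previous one-arm clinical trial and usability and feasibility studies on the Web- and mobile-based The-Optimal-Lymph-Flow".

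Under Recruitment Process the article states: "we plan to use the successful procedures of recruiting and consenting participants used by the PI and the team in the preliminary studies". The references given there include number 19, the 140-patient study.

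The control arm is meant to be without the programme: "patients will not have access to The-Optimal-Lymph-Flow program". Randomization and Blinding says that participants will not be told which of the two programmes is the one being tested.

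**The concern.** Followed as written, the plan can enrol a woman who was taught the exercises in the nurse-delivered study or who tested the Web system, provided she still reports pain. What is tested is a set of learned skills, which closing a section of the website does not remove.

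Two things are at stake. The first is the contrast. A pre-exposed woman in the intervention arm has less that is new to learn, so her expected gain is smaller. The second is participant blinding. A woman who has met the programme before could recognise it, or notice that she has not been given it, and the primary outcome is pain that she reports herself.

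Nothing else in the Methods would identify such women. Earlier receipt of the programme is not among the covariates under Outcome Measures and is not named as a factor in the randomisation. Data Collection Procedures and Outcome Measures place the self-care checklist at week 12 only. The Abstract can be read as placing it at baseline too, but the Methods do not carry that through.

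**Working it through.** **Inputs.** From Sample Size and Power Calculations: 60 enrolled per arm, 20% attrition, two-sided two-sample t test, alpha 0.05, power 90%, detectable difference 0.7 SD. From the Background: 140 and 30 women exposed earlier, so at most 140 + 30 = 170 if the groups are distinct. The share p of enrolled women who are pre-exposed is not in the documents and is varied below.

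**The plan's own figure.** Analysed per arm: 60 × 0.8 = 48. The detectable difference at 90% power is (1.960 + 1.282) × √(2/48) = 0.662 SD by the normal approximation and 0.669 SD by the noncentral t. Both round to the stated 0.7. At exactly 0.7 SD the noncentrality is 0.7 × √(48/2) = 3.43 on 94 degrees of freedom, and power is 0.924 (normal approximation 0.929). No stated figure is wrong.

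**Dilution.** Let a newly taught woman gain δ relative to a control woman. Randomisation puts the same expected share p of pre-exposed women in each arm. There are two simple ways in which such women could contribute nothing:

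- Her benefit is already in her baseline and she gains nothing further in either arm. The arm means are (1 − p)δ and 0, and the contrast is (1 − p)δ.
- She gains δ in either arm because she already has the skills. The arm means are δ and pδ, and the contrast is again (1 − p)δ.

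These are alternatives for a given woman and do not add up. Both lead to an effect of 0.7 × (1 − p), with the SD held at 1.

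| p | Women of 120 | Effect (SD) | Power, 48 per arm (t) | Enrolment per arm for 90% power, 20% attrition (normal) |
|---|---|---|---|---|
| 0 | 0 | 0.700 | 0.924 | 54 |
| 5% | 6 | 0.665 | 0.897 | 60 |
| 10% | 12 | 0.630 | 0.863 | 67 |
| 15% | 18 | 0.595 | 0.823 | 75 |
| 20% | 24 | 0.560 | 0.775 | 85 |
| 30% | 36 | 0.490 | 0.661 | 110 |

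Up to about 5% the loss is absorbed, because 0.669 was rounded up to 0.7. Power drops below 80% somewhere between 15% and 20%.

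**How demanding these shares are.** With at most 170 exposed women, p = 10% needs 12/170 = 7% of them to enrol again, and p = 20% needs 24/170 = 14%. If only half still had qualifying pain (an assumption), p = 20% would need 24/85 = 28%.

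**The case against.** The strongest reply is that the overlap is conjecture. Reusing recruiting procedures does not mean recruiting the same women. The article does not say where the earlier studies recruited, or that any participant was approached again. That stands, and it is why the power figures are a range and not an estimate.

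A reader might infer that the control arm will be contaminated by women who are in effect on the intervention. The documents do not support that. Every woman enters with pain, and the Analysis Plan judges the effect by the group-by-time interaction. A control woman who has practised steadily carries any benefit in her baseline and would be expected to change much as other controls do. Nor does any passage show that the exercises, once learned, are kept up for good; the daily reminders and the encouragement to exercise point the other way. The main mechanism is therefore the smaller gain among pre-exposed women in the intervention arm.

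Zero contrast is also a worst case. The comparator is an active Arm Precaution programme with its own exercise videos. The 140 patients had the content from nurses, not in the Web form under test, so they may still gain from the videos, app and reminders. Earlier users who became free of pain are excluded.

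Partial safeguards exist. The week-12 checklist would show breathing and pumping exercises among controls, and expectation of the programme and self-care behaviours appear among the covariates. None of these records earlier exposure. Practice at week 12 arises after randomisation and is what the programme aims to change, so adjusting for it is no substitute.

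Finally, a journal article condenses, and a fuller protocol might hold a further criterion. But eligibility appears here as a numbered list with no sign of abridgement.

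**Conclusion.** The gap is real and its size is unknown. The eligibility list admits women already taught or shown the programme, and the Methods would not identify them. If some enrol, the expected effect is dilution towards no difference. A reader might suspect a spurious benefit, but randomisation balances prior exposure on average, so that does not follow. Participant blinding is weakened for those women only; it is not defeated for the trial.

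Under the worst-case assumption that pre-exposed women contribute no contrast, equally in both arms and with the SD unchanged, the loss is negligible at 5%, about 6 percentage points of power at 10% (92% to 86%) and about 15 at 20% (92% to 78%). A smaller overlap or partial carry-over would cost less. This is a cheap improvement of low-to-moderate priority. The article does not contradict itself here and its sample-size figure is sound.

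**What to change.** Add one exclusion criterion: previous participation in any study or usability test of The-Optimal-Lymph-Flow, or previous use of the programme, website or app. The research coordinator checks the team's own study lists and asks the woman at the eligibility meeting described under Consent Process.

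Because recruitment is already open, record prior exposure for women already enrolled, using the earlier studies' lists where possible so that the classification predates randomisation and cannot depend on the arm. Repeat the primary analysis without the exposed women as a pre-specified sensitivity analysis. Prior exposure is a baseline characteristic, so leaving these women out keeps the comparison randomised.

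The cost is one eligibility line, one baseline question and a check of existing records, with the loss of a few otherwise eligible women from recruitment. The sensitivity analysis is smaller but need not be weaker. Removing 10% leaves 48 × 0.9 ≈ 43 per arm, with power 0.894 for 0.7 SD by the t formula, against 0.863 if those women stayed in and contributed no contrast.

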### Recruitment

#### Recruitment Process

Participants have been recruited face-to-face at point of care during clinical visits from New York University (NYU) Cancer Center. To accomplish recruitment of 120 participants, we plan to use the successful procedures of recruiting and consenting participants used by the PI and the team in the preliminary studies [3,9,14,17,19]. Successful strategies include the use of *Invitation Flyer* that describes the study. This *Invitation Flyer* is posted on the bulletin boards or breast cancer support website at the cancer center, and is also available in the reception areas of the cancer center, examination rooms, and rooms holding support group meetings. In addition, health care providers such as nurses, oncologists, breast surgeons, and oncology radiologists at the center are willing to refer women meeting the inclusion criteria to the study by distributing the *Invitation Flyer* that describes the study to the potential participants.

#### Consent Process

After reading the *Invitation Flyer*, if a woman is interested in participating in the study, she would schedule a meeting with the research coordinator at that time or at other convenient time for them. During the meeting, the research coordinator will confirm her interest, determine if the woman is eligible for the study and the research coordinator will again explain the study in detail and provide enough time for the woman to ask questions. If the woman agrees to participate, she will sign the consent form.

#### Confidentiality

Confidentiality will be maintained. Patients will be assigned a study ID specific for the study. Study data recording for the research will only use the study ID without the patients’ identifying information. A document file that has the patients’ study ID with the patients’ identifying information will be separately stored in locked files accessible only to the research coordinator, research nurse, or the PI. Electronic data will be stored in a password protected computer accessible only to the PI, the research nurse, and the research coordinator. Data analysis will be carried out and reported in the aggregate data so that individual identities are not revealed. Careful training and supervision of research coordinator and research nurse will insure study procedures are carried out in accordance with established protocols.

### Randomization and Blinding

The randomization assignment will be generated by our senior statistician using a computer-generated randomization procedure. Participants will be randomized based on their report of pain/aching/soreness or tenderness to be allocated to intervention and control group. The researchers who perform pre- and post-intervention measurements will be blinded throughout the study to the participants’ assigned arm. Participants will not know which intervention was the intervention of interest and which one was the comparator.

### Study Intervention

#### Overview

The Web- and mobile-based *The-Optimal-Lymph-Flow* [19,22] includes information about lymphedema, diagnosis and measurement of lymphedema, lymphatic system, risk of lymphedema, self-care, daily exercises, arm precautions, and ask experts. Participants in the intervention group will have access to the 8 Avatar videos that provide step-by-step instructions for The-Optimal-Lymph-Flow exercises to promote lymph flow and optimize shoulder and limb mobility. The platform also has a section entitled Arm Precautions, representing current patient education that emphasizes precautionary lifestyle behaviors, such as avoidance of repetitive limb movement, lifting weighted objects, needle punctures, blood draw, and the use of compression garments for air travel in the affected limb [20,21]. Figures 2-5 shows some screenshots of the The-Optimal-Lymph-Flow program. Table 1 presents the strategies, rationales, and actions for *The-Optimal-Lymph-Flow* program.

**Table 1 table1:** The-Optimal-Lymph-Flow program: self-care strategies, rationales, and actions

Strategies		Rationales	Actions
**Promoting lymph flow**			
	Muscle-tightening deep breathing	The whole body lymph fluid has to be drained through the lymphatic ducts above the heart. Muscle-tightening deep breathing stimulates lymphatic ducts and help lymph fluid drain.	At least twice a day in the morning & at night before brushing teeth or as much as the patient wants throughout the day.
		Lymph fluid drains when muscles move. Muscle-tightening deep breathing creates the whole body muscle movements that create muscle milking and pumping action and help to drain lymph fluid.	Air-travel: before take-off and after landing.
			Sedentary lifestyle: at least every 4 hours.
	Muscle-tightening pumping	Muscle-tightening pumping exercises create arm muscle pumping. This helps lymph fluid flow and decreases the fluid build-up in the arms.	At least twice a day in the morning & at night before brushing teeth or as much as the patient wants throughout the day.
		Muscle-tightening pumping exercises build the arm muscle that helps lymph fluid flow and drain.	Air-travel: before take-off and after landing.
			Sedentary lifestyle: at least every 4 hours.
	Large muscle exercises: walking, marching at home, dancing, swimming, Yoga, Tai Chi	Large muscle exercises create muscle milking and pumping to promote overall body lymph fluid flow and drain.	At least 10-minutes daily.
			Air-travel: get up and walk around for flight over 4 hours.
			Sedentary lifestyle: get up and walk at least every 4 hours.
**Improving limb functional status**			
	Shoulder exercises	Improved limb mobility after surgery facilitates local muscle movements that create muscle milking and pumping to promote local limb lymph fluid flow and drain.	One week after surgery if there is no surgical drains or after the surgical drains are removed.
			At least twice a day until limb functions are returned to normal.
			Whenever limb mobility is limited throughout the recovery.
**Keep a healthy weight**			
	Eat nutrition-balanced diet (ie, more vegetables and fruit as well as quality proteins); Maintain portion-appropriate diet (feeling 75% full for each meal)	Overweight or obesity is an important risk factor for lymph fluid accumulation.	Each meal daily
		Having extra weight makes it difficult for lymph flow and drain. This can lead to extra lymph fluid build-up.	It is important to talk to the nutritionist who can help to find proper weight reduction programs.
		There are numerous weight management programs available to assist with weight loss.	
		Although there are a lot of weight reduction programs, each person may respond differently to each program.	
		The core of the weight management is to eat a nutrition-balanced, portion-appropriate diet. It is also important to stay hydrated, exercise, and get adequate sleep.	
	Stay hydrated	People may actually be thirsty, not hungry.	Drink 6 to 8 glasses of water daily; in the morning, before and during meals, and throughout the day.
			Avoid drinks with calories (eg, juices).
			Drink green tea to boost metabolism.
	Large muscle exercises	Daily large muscle exercises (eg, walking, running, swimming, Yoga) help to burn more calories.	At least 30-minutes 3 times a week or daily.
		Daily large muscle exercises also promote lymph flow by creating muscle pumps.	
	Get enough sleep	Lack of sleep increases the production of the stress hormone cortisol, creates hunger, and leads to overeating.	At least 7-8 hours of sleep per night.
		Getting just one more hour of sleep per night reduces belly fat accumulation.	

